### Study Summary

This study is a community-based randomized trial of an intervention to prevent maternal depression in Head Start. The intervention is Problem Solving Education (PSE). We are conducting an efficacy RCT with a total enrollment goal of 230 Head Start mothers at risk for depression (not with major depressive episode, MDE).

This study is operationally linked to two other pilot studies, which draw their participants from the same recruitment infrastructure: a pilot study of how to engage a separate population of Head Start mothers *with MDE* into care; and an administrative supplement-funded pilot of an abridged, or simplified, version of PSE (referred to as PSE-lite), delivered to Head Start mothers with the same characteristics of those participating in the larger clinical trial (a schematic representation of how these three studies interact is provided in the study binder). In the current RCT, we use PSE to prevent depression in mothers at risk for depression.

Considering the three studies, the following represent key steps in the overall protocol:

1. Screening and risk stratification before the written informed consent process to determine if a subject, at baseline, is 'at risk' for depression, or has MDE.
2. Of the 'at risk' subjects, most will be offered participation in the prevention RCT. Of these, half will receive PSE. The other half will not receive PSE, but will be referred to further care when appropriate per usual Head Start mechanisms (i.e. the control group will receive usual Head Start services).
3. A small number of 'at risk' subject will be offered participation in the supplementary pilot of PSE-lite. These individuals represent participants over and above the 230 projected to enroll in the trial.
4. Those in MDE will be routed to Engagement with Care pilot study. This study aims to navigate depressed mothers into more definitive mental health care; it is a separate study, but will share research staff (for both recruitment/enrollment and outcome assessment).
5. If at any point during the prevention study, any mother has high depressive symptoms, we will offer a referral to more definitive mental health care.

### Background/Rationale/Purpose

Depression is common among young, low-income mothers and has negative repercussions on children. Additionally, this population of mothers lacks access to quality mental health services – making a prevention intervention potentially important. We are conducting a multi-year RCT of a Head Start-based intervention model developed as part of [name] and [name] K23 awards. PSE represents an integrated identification and intervention system based on the construct of screening, brief intervention, and referral to treatment (SBIRT). Within the case management services of Head Start, eligible mothers will be randomized to receive either usual care or PSE. The basic steps of PSE are: screening to determine the severity of one's depressive symptoms; a problem-solving intervention

for those at risk for depression; and referral to more definitive services for those initially in the at risk group, who have worsening symptoms over time.

The specifics of PSE have been modified and field-tested over the previous four years (primarily in Head Start, under another BUMC IRB protocol H-25084). Activated referrals to further care incorporate principles of motivational enhancement that have been demonstrated to improve engagement with care in other settings and for other medical conditions. We will conduct an efficacy RCT, involving 230 Head Start mothers. Over a 12-month follow up period, we aim to:

1. Improve mothers' problem solving skills (primary outcome)
2. Decrease the incident rate of episodes in which mothers experience moderate to severe depressive symptoms and reduce depressive symptoms over time (primary outcome)
3. Increase mothers' likelihood of engaging with primary care or specialty mental health services if referred (secondary outcome)
4. Improve parental functioning, as assessed by children's missed Head Start school days (secondary outcome).

## Subjects

### Inclusion Criteria

Based on the paradigm of the 1994 IOM report on preventing mental disorders, we have designed PSE to be a risk-prevention intervention - designed to prevent depression among mothers *known to be at risk*. The IOM calls this a 'selective' prevention strategy. PSE has already been adapted for mothers of young children, who represent our population of interest.

#### Summary of inclusion criteria

1. Family enrolled in Head Start, and child expected to attend Head Start activities for at least 6 months of the 12- month follow-up period.
2. Family without imminent plans to relocate
3. Mother is comfortable in English or Spanish.
4. Parent/guardian who has a child that attends Head Start
5. Child attending Head Start and is between the ages 0-5
6. Screen positive to 2-question depression screener (PHQ2), or have a past history of depression
7. Screen Negative for current MDE using the M.I.N.I MDE Module.
8. Ability to provide informed consent.
9. Not suicidal

#### Details of Inclusion Criteria

Based on previous work aiming to prevent major depression, we will initially select at-risk mothers

using two criteria: 1) a recent history of depression, or 2) current subsyndromal depressive symptomatology. This screening component (a 5 question screener) will be embedded within Head Start caseworkers' Strength and Needs Assessment of Head Start families. The primary purpose of this is to screen people *into* the study.

Mothers who are positive on this initial recruitment screen will be called by research staff and will be asked permission for a second screen to determine if they are currently (past 2 weeks) in a Major Depressive Episode using the M.I.N.I. MDE Module. The primary purpose of this is to screen people *out* of the study.

Only mothers who are both positive on the 5 question recruitment screen AND who are MDE negative in the past 2 weeks will engage in formal written informed consent.

Immediately after the written informed consent process (described later), we will use the MacArthur Competence Assessment Tool for Clinical Research (MacCAT-CR) to determine the potential subject's capacity to consent to research. This screening tool will screen out any mothers who are psychotic, or impaired in their capacity to participate in a research study. The MacCAT-CR thus serves the dual purpose of confirming one's ability to provide informed consent and screening out thought-disordered individuals from a study that is not appropriate for them.

Next, we will use the MacArthur Suicide Screening Questions to assess suicidal ideation at low, intermediate or high risk. We will only accept mothers into the study who are at low or intermediate risk for suicide. This means that either mothers with no current thoughts or with current thoughts but no plans of suicide will be eligible for participation. The reason for this exclusion criterion is participant safety. Our plans to manage a crisis brought on by the expression of suicidal ideation are also detailed in our attached protocols.

## **Exclusion Criteria**

### Summary of Exclusion criteria

1. High suicidal ideation (McArthur Suicide Screen)
2. Cognitive limitation (McCAT-CR)
3. Psychosis
4. No known risks for depression (based on recruitment screener)
5. Positive for MDE on the M.I.N.I. MDE Module (Note that MDE Positive individuals will be referred to participate in study outlined in protocol H-31676).
6. Mothers who have plans to leave the State of Massachusetts and/or the Country during the 12-month period of the study for more than 2 months will be excluded from the study for safety and research follow up reasons. These mothers will be included in the next wave of recruitment.

### Details of Exclusion Criteria

Mothers who are NOT at risk for depression based on current symptoms and past history of depression illness be excluded from the study based on the recruitment screen. These mothers would not benefit

from a prevention trial (PSE) since they are not at risk for depression. Similarly, mothers with MDE will not be eligible.

In addition, we will exclude mothers who cannot give capacity to consent because of either cognitive limitation or psychosis by using the MacCAT-CR. We will also exclude mothers with high suicidal ideation by using the MacArthur Suicide Screening Questions. Both of these measures have been used widely in other research studies to protect vulnerable populations.

### **Subjects – Demographic Characteristics and Vulnerabilities**

For regulatory purposes, we will indicate to the IRB that we will be interacting with the following vulnerable populations and populations requiring special protections:

1. Adolescents, ages 15-17
2. Adults, ages 18-64
3. Children, ages less than 7
4. Minors independently making their own healthcare decisions
5. Pregnant women
6. Women of child bearing potential
7. Women with depression or symptoms of depression could be considered a vulnerable population

Children less than 7 years constitute study subjects because parents and Head Start teachers will be asked to fill out the Social Skills Rating System with reference to 3-5 year-old children of the adult study subjects. Additionally, some of the women recruited in our study may be of childbearing potential, may be pregnant or may be emancipated minors (e.g. teen mothers). The following will be explained in our IRB protocol:

**INFORMED CONSENT:** The consent form will be explained in very basic language, and mothers will be given ample opportunity to ask questions and/or opt out of the study. We will ask permission for teachers to answer questions about their children, and they may still be in the study and not give us permission to do so.

**CONFIDENTIALITY:** We will apply for a federal certificate of confidentiality. Mothers will also be informed that all data collected will be strictly confidential. All data collected will be stripped of identifiers and assigned a unique study code.

**UNDUE COERCION:** All subjects will be explained that their participation is completely voluntary, and that they have the right not to participate. They will be explained that even if they do not participate, project staff will do everything it can to help them with any symptoms of depression that they may have. They will be explained that should they not want to participate, no benefit that they have will be affected. They will be explained that they may drop out of the study at any point, should they chose to do so, and that no questions will be asked. Study personnel will also be happy to assist them in accessing further care.

**PROTECTIONS FOR WOMEN OF CHILD BEARING POTENTIAL/PREGNANT WOMEN** Women of child bearing potential or pregnant women will be entitled the same protections as listed above. We

foresee no extra risk of the study for a woman of child bearing potential than it is to anyone else.

### Design

At present, all Head Start mothers are given social work and case management services and education by the Head Start team regarding the importance of physical and mental health care. Mothers are screened for mental health needs during their "strength and needs assessment" by the case management staff and given referrals to care when necessary. However, there is no systematic depression prevention strategy, and there is no tested, evidence-supported mechanism to get depressed parents quality mental health care.

Study design. Parallel group, RCT involving mothers whose children attend Head Start - a comprehensive preschool program for low-income children birth to 5. Eligible mothers will be randomized to receive PSE or standard of care at Head Start. Both groups will be followed for 12 months.

Participants. 230 Head Start mothers (115, PSE; 115, control) will be enrolled in the at-risk stratum.

Randomization. The unit of randomization will be the mother. Investigators and data collectors will be blinded to study allocation. We could have chosen a number of study designs, including cluster randomization by caseworker or Head Start center. Cluster randomization, however, has its own set of methodologic shortcomings, notably post-randomization selection bias. Because we also expect high intra-class correlation among families within the same Head Start center, a cluster design on this basis would create unrealistic sample size requirements. Conversely, the only substantial drawback of a parallel design would be a conservative bias in favor of the control arm due to intervention spillover. However, because control subjects will not have access to trained educators, we anticipate such effects to be minimal. Randomization will occur independently within each Head Start site, within strata defined by the presence or absence of depression history. We will randomize 1:1 within randomly varying blocks of 2 and 4.

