8. Outcome assessments: Each subject will have a 12-month follow up period, during which blinded research assistants will assess outcome measures. Follow-up data collection will begin 2 months after baseline because a full, 6-session course of PSE typically lasts 6-8 weeks. To limit attrition, we will employ a combination of monetary incentives and postcard reminders. Through these strategies, approved by the BUMC IRB in our pilot work, we have been able to maintain follow up rates > 85% across all relevant ongoing studies (there is a separate section on participant compensation in the protocol manual).

Baseline, 6-month, and 12-month assessments will take place in person with a staff RA. We will administer the QIDS and mental health service use questions on a bimonthly basis throughout the study period, and this will be done by telephone by a staff RA.

The 6-month interview will comprise the following valid and reliable scales:

- a. Perceived Stress Scale
- b. M.I.N.I. Depression Module
- c. QIDS
- d. Mental Health Service Use questions (adapted from Collaborative Psychiatric Epidemiology Surveys)
- e. Social functioning (Social Adjustment Scale-Self Report)
- f. Parenting Stress Index
- g. Problem Solving Questions (Social Problem Solving Inventory)
- h. Coping Questions (Brief COPE)
- i. Pearlin Mastery Scale
- j. Behavioral Activation for Depression Scale
- k. Rosenberg Self-Esteem Scale

The 12-month interview will comprise the following valid and reliable scales:

- a. Perceived Stress Scale
- b. M.I.N.I. Depression Module
- c. QIDS
- d. Mental Health Service Use questions (adapted from Collaborative Psychiatric Epidemiology Surveys)
- e. Social functioning (Social Adjustment Scale-Self Report)
- f. Problem Solving Questions (Social Problem Solving Inventory)
- g. Coping Questions (Brief COPE)
- h. Pearlin Mastery Scale
- i. Behavioral Activation for Depression Scale
- j. Rosenberg Self-Esteem Scale
- k. Recent Life Changes Questionnaire

- I. Mood, anxiety and alcohol and other substance use, modules of the SCID

RA's will be trained not to leave telephone messages, and to introduce themselves as from "BMC" so as to ensure confidentiality.

9. At 6-months post randomization, parents and Head Start teachers will be asked to fill out the Social Skills Rating System (SSRS) with reference to all 3-5 year-old Head Start children of enrolled parents.
10. We will assess rate of absenteeism from Head Start for children of mothers who are in our study.

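### No eligibility criterion excludes mothers already taught PSE in the earlier Head Start field test, so a pre-taught mother can be randomized to control; any effect is toward the null and of unknown size

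*Protocol*

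**What the plan says.** Background/Rationale/Purpose states that the specifics of PSE "have been modified and field-tested over the previous four years (primarily in Head Start, under another BUMC IRB protocol H-25084". The Protocol does not say how many mothers were taught, at which sites, or when the work ended.

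The Summary of inclusion criteria has nine items. Those that define the target population are "Screen positive to 2-question depression screener (PHQ2), or have a past history of depression" and a negative screen for a current major depressive episode. The child criterion is "Child attending Head Start and is between the ages 0-5". The Summary of Exclusion criteria has six items: high suicidality, cognitive limitation, psychosis, no known depression risk, a current major depressive episode, and planned absence from the state or country. Neither list, nor the two sections giving their details, mentions earlier receipt of PSE.

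The list kept to avoid approaching a mother twice (Procedure and Consent Procedures) holds mothers who refuse, are ineligible or decline during this trial's own recruitment. The baseline battery in Procedure includes questions on mental health service use, but no measure is described as recording prior PSE.

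On contamination, the Design section says that "the only substantial drawback of a parallel design would be a conservative bias in favor of the control arm due to intervention spillover", and then that "because control subjects will not have access to trained educators, we anticipate such effects to be minimal".

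**The concern.** The contamination argument covers one route only: a control mother meeting a trained educator, or someone taught by one, during the trial. PSE teaches a skill, and problem-solving skill is itself a primary outcome. A mother who learned it in the field test needs no educator in order to use it. If she meets the other criteria she is eligible, and with 1:1 allocation she is as likely to be a control as a PSE mother.

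At stake is the contrast between PSE and a control arm that the sample size treats as untaught. Because no baseline item is described as recording prior exposure, the trial might also be unable to show afterwards how much of it there was.

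**Working it through.** **Inputs.** All are from Sample Size Justification unless marked.
- Two-sided alpha 0.05, 80% power, 100 analysable mothers per group.
- SPSI-R: SD 2.5, difference 1 point (0.4 SD), two-sample t-test.
- Episodes: Poisson rate 1.2 in control against 0.8 in PSE, per five follow-up assessments.
- Share f of controls previously taught PSE: **not given**. A range of 0 to 20% is assumed.
- Carry-over: **not given**. Full and lasting carry-over is assumed, with the PSE-arm mean unchanged. This is the worst case for a given f.

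**Reproducing the plan.** For SPSI-R, n per group = 2 × (1.96 + 0.84)² × 2.5² / 1² ≈ 98.1, which rounds up to 99; the stated 100 is confirmed. The exact t-test at 100 per group gives 80.4% power. For episodes, the expected counts are 120 and 80, so z = ln(1.5) / √(1/120 + 1/80) = 0.4055 / 0.1443 = 2.81, and power = Φ(2.81 − 1.96) = 80.2%. Both figures sit almost exactly at 80%. Nor is there a cushion in the number randomized: 230 × 0.85 = 195.5 after the plan's 15% attrition.

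**Effect of pre-taught controls.** With a share f of controls already at the PSE-arm level, the SPSI-R difference becomes 1 × (1 − f) and the control episode rate becomes 1.2 − 0.4f.

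| f | SPSI-R difference | SPSI-R power (t-test) | n per group for 80% (normal formula) | Control episode rate | Poisson power |
|---|---|---|---|---|---|
| 0 | 1.00 | 80.4% | 99 | 1.200 | 80.2% |
| 1% | 0.99 | 79.6% | 101 | 1.196 | 79.5% |
| 2% | 0.98 | 78.8% | 103 | 1.192 | 78.8% |
| 5% | 0.95 | 76.2% | 109 | 1.180 | 76.5% |
| 10% | 0.90 | 71.7% | 122 | 1.160 | 72.5% |
| 20% | 0.80 | 61.5% | 154 | 1.120 | 63.3% |

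The loss is about 1 to 2 points at 1 to 2% exposure, 4 points at 5%, 8 to 9 points at 10% and 17 to 19 points at 20%. If only part of the effect persists, f is in effect multiplied by that part: 10% of controls with half carry-over behaves like the 5% row. The QIDS outcome over time was not computed; the direction would be the same.

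**The case against.** The strongest answer is that the harm depends on a quantity that the Protocol does not supply. There is no count of mothers taught, no statement that the field test used the same sites, and no information on how long the skill lasts. The criteria also limit overlap. A prior recipient must now have a child of 0 to 5 attending Head Start, must screen at risk, and must not be in a major depressive episode. Many field-test families will have moved on, although a child enrolled during those four years may still be young enough and a later sibling can qualify. All this stands, and it is why the size is given only as a range.

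The Design statement about educators is also not false. It weighs spillover within the trial when choosing individual over cluster randomization. It simply does not reach exposure before the trial.

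A reader might infer more than the documents support:
- That the PSE-versus-control difference is in fact diluted. The documents show that it can be, not that it is.
- That mothers with symptoms or past depression were the typical field-test users. Eligibility under H-25084 is not described.
- That the retention statement, "we have been able to maintain follow up rates > 85% across all relevant ongoing studies", shows other studies teaching PSE. It is cited for follow-up rates only, and the team also ran an observational cohort.
- That a re-taught mother in the PSE arm adds further dilution because she has less to gain. The planned test compares mean scores between groups. Under full carry-over she still has the treated follow-up mean.
- That concurrent PSE-lite, or a second randomization in a later wave, is an open route. Consent Procedures randomizes each mother to either the supplement or this trial. The mention of a next wave concerns mothers deferred for travel. Re-randomization is speculation.

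**Conclusion.** The gap in eligibility is real: as written, the plan admits pre-taught mothers to the control arm, does not describe any means of recognising them, and offers a contamination argument that does not apply to them. Randomization balances such mothers across arms in expectation, so the comparison is not confounded. Assuming earlier PSE acts in the same direction as trial PSE, the contrast can only move toward the null.

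The size cannot be fixed from the documents. At 1 to 2% exposure the loss is trivial; at 10% with full carry-over, SPSI-R power is about 72% and 122 per group would be needed to restore 80%. The concern is worth acting on mainly because the design has no spare power and the remedy is cheap, not because material dilution has been shown.

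**What to change.** Add one item to the Summary of Exclusion criteria: previous receipt of PSE (H-25084) or PSE-lite (H-31999). Ascertain it with a question at the research assistant's second verbal screen, before written consent. The study team's own participant lists can be used where the consent terms allow; matching against another protocol's list would have to be squared with the limited-use statement planned for the verbal consent (Recruitment Procedures).

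If any such mother has already been randomized, keep her in the intention-to-treat set, report prior exposure by arm, and add a sensitivity analysis without these mothers. In the Design section, say that the spillover argument refers to exposure during the trial and that earlier exposure is handled by the exclusion.

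The cost is one eligibility line, one question and the loss of a few otherwise eligible mothers. If there is no overlap, no mothers are lost.

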### Sample Size Justification

Based on empiric longitudinal data that we have collected among a cohort of Head Start mothers, we describe the size of detectable interventional effects with adequate statistical power for each primary outcome. All estimates assume 80% power and a two-sided alpha of 0.05.

- i. Problem solving skills. The mean problem solving (SPSI-R) score among mothers in our observational study is 12.2, (SD 2.5); women with  $\geq$  moderate depression symptoms have a mean score of 14.7 (SD 2.2) and those with  $\leq$  mild symptoms have a mean score of 9.8 (SD 2.8;  $p > 0.0001$ ). Using a two-sample t-test, a sample size of 100 per group will be able to detect a very granular one-point difference in mean SPSI-R scores between study groups (a standardized effect size of 0.4).

- ii. Incident rate of moderate to severe symptomatic episodes. Using poisson regression analysis, with 100 subjects in each study group and a poisson rate of 1.2 spikes per 5 follow-up assessments in the control group (according to our current data), we can detect a reduction in the rate of spikes to 0.8 in the treatment group – a 33% reduction in symptomatic episodes.
- iii. Depressive symptoms over time. In our longitudinal data, we have observed the following mean QIDS scores for each follow-up month and assume these values for the control group in the planned study: 8.2; 7.6; 7.5; 6.9; 7.2 (common SD, 5.9). We hypothesize that the following mean QIDS scores in the treatment group would be achievable and clinically significant: 7.2; 6.6; 5.5; 4.4; 4.2, resulting in a mean difference of 3 points in QIDS scores across study groups (note: a 3-point difference in QIDS scores, in the majority of cases, would move a subject across a clinical cutoff corresponding to mild, moderate or severe symptoms). Using a two group repeated measures design analyzed by generalized estimating equations or mixed linear models, noting within-subject correlations of 0.7 for values separated in time by one month and 0.6 for those separated for two months or more in our longitudinal analysis), we can detect the above differences in the means between groups over time with 100 subjects per study group.

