### Data Analysis

Our analysis plan conforms to CONSORT guidelines. We will record the number of families approached, screened, ineligible, and refusing participation. We will assess the success of randomization by comparing baseline characteristics between groups. We will record subject attrition and note all adverse events. To estimate intervention effect, we will conduct an intention-to-treat analysis to compare the difference between intervention and control groups for all primary and secondary outcome measures. The following primary outcomes will be analyzed accordingly:

- i. Problem solving skills. We will employ two sample t-tests to compare mean problem solving scores between groups. If significant baseline differences exist across groups, we will employ linear regression analysis to adjust for these differences.
- ii. Incident rate of moderate to severe symptomatic episodes. We will employ Poisson regression techniques to compare rates of elevations in QIDS scores to  $\geq 11$  (moderate symptomatology) over the 12 months of follow-up.
- iii. Depressive symptoms over time. We will use generalized estimating equations or mixed linear models to examine group-by-time effects on mean QIDS scores over the 12 months of follow-up.

Using generalized mixed models for each of these outcomes (to which the above analytic methods can be extended), we will also investigate the impact of Head Start enrollment site as a clustering effect. As an exploratory analysis, we will also examine additional clustering of PSE clients by educator.

This analysis plan, taken from our grant application, will be reproduced in our IRB application.

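### The problem-solving primary outcome is tested with an unadjusted t-test after randomisation stratified by site and depression history, so its intervals are wider than they need to be

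*Protocol*

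**What the plan says.** On randomisation, the Protocol's Design section says: "Randomization will occur independently within each Head Start site, within strata defined by the presence or absence of depression history". The next sentence adds: "We will randomize 1:1 within randomly varying blocks of 2 and 4". The same paragraph rejects cluster randomisation partly because "we also expect high intra-class correlation among families within the same Head Start center". Under the inclusion criteria, past depression is one of the two routes by which a mother counts as at risk.

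The Data Analysis section names one method for each primary outcome:
- a two-sample t-test for problem-solving scores, with linear regression only if the groups differ significantly at baseline;
- Poisson regression for the rate of moderate-to-severe symptom episodes;
- GEE or a mixed linear model for group-by-time effects on mean QIDS.

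None of the three names site or depression history. After the list, the section says that, with generalised mixed models for each outcome, "we will also investigate the impact of Head Start enrollment site as a clustering effect". Depression history does not appear in that section. The January 2018 Appendix adds coping style and the degree of baseline depressive symptoms as moderators, but not depression history.

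The Sample Size Justification rests on the same unadjusted test: "a sample size of 100 per group will be able to detect a very granular one-point difference in mean SPSI-R scores between study groups".

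**The concern.** Stratified blocks force the arms to be nearly balanced within each site-by-history cell. Differences between cells then contribute almost nothing to the chance variation of the treatment difference. A t-test that ignores the cells still counts that between-cell variation as error, so its standard error is too large. The test runs below its nominal 5% level and the interval is too wide.

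The conditional adjustment rule does not repair this. It is triggered by imbalance, and the stratifiers are the variables least likely to be imbalanced. A covariate matters here because it predicts outcome and was used in the allocation, not because it happens to differ between arms.

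At stake is precision on one primary outcome that the allocation scheme has already made available. The Protocol itself expects site to matter, since it uses high within-centre correlation as a reason against another design.

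**Working it through.** **The plan's own figures.** The Sample Size Justification says: "All estimates assume 80% power and a two-sided alpha of 0.05". For SPSI-R it uses SD 2.5, a 1-point difference and 100 per group, so d = 1/2.5 = 0.4. The expected z is 0.4 × √(100/2) = 2.828, and power = Φ(2.828 − 1.96) = Φ(0.868) = 80.7%. The exact noncentral t gives 80.4%, with n = 100 per group. The stated figure reproduces, and it is the power of an unadjusted test.

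**Effect of omitting the strata.** Let ρ be the share of SPSI-R variance lying between strata. The Protocol gives no value, so ρ is an assumption, shown here from 0.01 to 0.30. With allocation balanced within strata:
- true variance of the difference = (1 − ρ) × 2σ²/n, whereas the t-test uses 2σ²/n;
- excess interval width = 1/√(1 − ρ) − 1;
- true type I error = 2 × [1 − Φ(1.96/√(1 − ρ))];
- t-test power = Φ((2.828 − 1.96)/√(1 − ρ));
- power with strata in the model = Φ(2.828/√(1 − ρ) − 1.96).

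The t-test's 95% half-width is 1.96 × 2.5 × √(2/100) = 0.693 points. The adjusted half-width is that figure times √(1 − ρ).

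| ρ (assumed) | Interval too wide by | True type I error | Adjusted half-width | Power, t-test | Power, adjusted |
|---|---|---|---|---|---|
| 0.01 | 0.5% | 4.9% | 0.689 | 80.9% | 81.1% |
| 0.05 | 2.6% | 4.4% | 0.675 | 81.4% | 82.7% |
| 0.10 | 5.4% | 3.9% | 0.657 | 82.0% | 84.6% |
| 0.20 | 11.8% | 2.8% | 0.620 | 83.4% | 88.5% |
| 0.30 | 19.5% | 1.9% | 0.580 | 85.0% | 92.2% |

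For ρ = 0.10, √0.9 = 0.9487. The t-test gives Φ(0.868/0.9487) = Φ(0.915) = 82.0%, and the adjusted test gives Φ(2.828/0.9487 − 1.96) = Φ(1.021) = 84.6%.

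**Simulation.** The closed form assumes perfect balance within strata. It was checked with 200 mothers, 4, 6 or 10 sites × 2 history strata, blocks of 2 and 4, and 4,000 runs per setting (Monte Carlo standard error near 5%: √(0.05 × 0.95/4000) = 0.3 points).
- ρ = 0.20: the t-test's type I error was 3.0% to 3.3%. Power was 82% to 84% unadjusted and 88% to 89% adjusted.
- ρ = 0.10: type I error was 3.8% to 4.1%.
- ρ = 0.05: type I error was 4.0% to 5.5%, so at that strength the simulation does not clearly separate the t-test from nominal.

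**The other two primary outcomes.**
- *Poisson.* The planning input is "with 100 subjects in each study group and a poisson rate of 1.2 spikes per 5 follow-up assessments in the control group", against 0.8 under treatment. Power = Φ(ln 1.5/√(1/120 + 1/80) − 1.96) = Φ(2.809 − 1.96) = 80.2%, which also reproduces. A plain Poisson model takes its variance from the mean and does not absorb between-stratum spread. With strata omitted and no further overdispersion, simulated type I error was 4.8% to 5.3% and power 79% to 81%.
- *QIDS group-by-time.* A stratum effect that is constant over time cancels in a contrast of change over time. Simulated type I error for a group difference in slope was 4.5% to 6.0%, with no conservative trend.

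**The case against.** The strongest reply has five parts.

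1. **Site is not ignored.** The Data Analysis section already plans mixed models with site for every primary outcome. This stands. The question for site is only whether that model is primary or additional. It does not cover depression history.
2. **Planned power is not lost.** The trial was sized on the unadjusted test, and in the table t-test power stays above 80% and rises with ρ. This also stands. The error is conservative, with no bias and no excess of false positives.
3. **The size rests on an unstated correlation.** The Protocol's expectation of high correlation is a remark about cluster designs, not an estimate for SPSI-R, and the number of sites is not given. At ρ = 0.01 the gain is 0.2 power points; a gain of about 5 points needs ρ near 0.20. This stands as a limit on the size, not on the direction.
4. **Covariates can be left to the SAP.** That is fair for the Poisson and QIDS models, where the Protocol names model families and excludes no terms. It does not answer the point for SPSI-R, where the Protocol fixes the unadjusted test and the condition for departing from it.
5. **The loss is not general.** A reader might infer that all three primary outcomes have over-wide intervals and lose power. The documents do not support this. The mechanism does not operate in a plain Poisson model, nor in the group-by-time contrast that the Protocol specifies. It could arise with robust or overdispersion-scaled standard errors for the episode rate, or with a time-averaged group effect on QIDS, but the Protocol commits to none of these.

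**Conclusion.** The point holds for the problem-solving outcome. The Protocol randomises within site-by-history strata, then fixes a test that leaves both factors out and an adjustment rule that balanced stratifiers will rarely trigger. The consequence is a mildly conservative test. For assumed between-stratum shares of 5%, 10% and 20%, intervals are about 3%, 5% and 12% too wide, and about 1.3, 2.6 and 5.1 power points are forgone (82.7 − 81.4, 84.6 − 82.0, 88.5 − 83.4). Those shares are assumptions; below about 10% the gain is small. The figures also assume 100 analysable mothers per group and near-complete balance within strata.

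It would be wrong to conclude that the trial is underpowered, that false positives are inflated, that site is left unmodelled, or that the episode-rate and group-by-time analyses suffer the same loss. For those two outcomes the case for including the strata is consistency with the randomisation, not a demonstrated loss.

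**What to change.** In the Data Analysis section of the Protocol:
- Replace the t-test for SPSI-R with a linear or linear mixed model that contains study arm, Head Start site (random or fixed intercept) and depression-history stratum as recorded at randomisation, all pre-specified.
- Delete the rule that makes adjustment depend on significant baseline differences.
- For consistency with the randomisation, put the same two terms in the Poisson and QIDS models, and make the model with site the primary analysis of each outcome rather than an additional one. The exploratory look at clustering by educator can stay as it is.

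The sample size need not change, because the unadjusted calculation already meets 80% power and adjustment can be expected to match or improve on it. The cost is wording only: both factors are known for every mother at randomisation, and no new data are needed. The change should be made before outcomes are compared by arm.
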